#### Cost assessment

The main outcome for cost is the incremental cost-effectiveness ratio (ICER). The ICER is measured as the total cost per quality-adjusted life-year (QALY) gained from baseline to follow-up. It is anticipated that telehealthcare will increase the participants’ quality of life, but no difference in mortality is expected. Additionally, it is expected that telehealthcare will reduce cost, particularly due to a reduction in the number of admissions/readmissions and outpatient visits [20].

### Sample size

A sample size calculation for effectiveness was performed using OpenEpi (http://www.openepi.com/Menu/OE_Menu.htm). Conservative estimates were applied for the minimal clinically important difference (change equal to 5 for the SF-36 physical component summary). With a power of 80%, groups of equal size, a standard deviation of 15, and a two-sided *p* value of <0.05, the required sample size is estimated to be at least 284 participants. With an expected loss to follow-up of 10%, the total required sample size is estimated to be at least 316 participants.

### Statistical methods

Statistical analysis will be conducted using an intention-to-treat standard. The results will be presented according to the Consolidated Standards of Reporting Trials (CONSORT) statement for randomized clinical trials [21]. Missing data will be assessed to identify patterns of missing data. Multiple imputation will be used if necessary, and the observations will be described according to epidemiological guidelines [22]. If appropriate, an adjustment will be made for differences between the intervention group and the control group with regard to baseline characteristics.

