### Recruitment

Recruitment takes place in three outpatient healthcare centers in the North Denmark Region (Aalborg University Hospital, Vendsyssel Hospital, and Thy-Mors Hospital). The recruitment includes both newly diagnosed patients and people with an existing diagnosis of HF. For pragmatic reasons, recruitment will be consecutive; that is, the first patients recruited in the project will receive the intervention for a longer time span than those included later in the process. Clinic staff will be responsible for identifying potential participants and assessing eligibility when participants are in contact with the outpatient healthcare center for other reasons. The clinical staff are responsible for telling the patient about the trial, and a printed folder with information is handed to the patient. All relevant clinical staff have been informed in meetings by the trial administration and have been supplied with written information about how to identify potential participants and how to include them.

The outpatient healthcare centers will send signed informed consent forms, together with the patient questionnaires and baseline physical measurements, to the trial administrators. The patient questionnaires include questions about the participants’ baseline health-related quality of life (Kansas City Cardiomyopathy Questionnaire [KCCQ], EuroQol EQ-5D-5L questionnaire, and Short Form Health Survey [SF-36]) and demographic characteristics (age, sex, education level, comorbidities, smoking habits, marital status, and job status). The patient questionnaires are completed at the outpatient healthcare center before each patient is assigned to the telehealthcare (intervention) group or usual healthcare (control) group. If the patient feels more confident in answering the questionnaire at home, this will be possible. All primary outcome data will be entered electronically. Original study forms will be entered and kept on file.

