### Randomization

The randomization of patients to either telehealthcare (intervention) or usual healthcare (control) is performed at the outpatient center after the patients have signed informed consent forms. Patient assignments are made using prepacked bundles of ten envelopes, each with a card, with assignment of five patients to the intervention group and five to the control group. Each prepacked bundle of ten envelopes is shuffled. In the outpatient healthcare center, a prepacked bundle is chosen to be the active bundle (i.e., the bundle used for assigning patients at random). When three envelopes are left in an active bundle, they are shuffled into a new bundle, and this new bundle is used as the active bundle.

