#### Effectiveness

To evaluate effectiveness, differences between the intervention group and the control group with regard to SF-36 scores, mortality rates, and physical measurements from baseline to follow-up will be analyzed. The outcome will primarily be analyzed using two-sample paired statistics (e.g., two-sample paired *t* test), such that the differences from baseline to follow-up will be assessed between groups.

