#### Cost assessment

To evaluate economic consequences, a health economic evaluation will be conducted. This will include the estimation of an ICER to summarize the cost-effectiveness of the telehealthcare intervention compared with the control group treatment. The ICER is defined as the difference in cost between two possible interventions, divided by the difference in their effect. The ratio represents the average incremental cost associated with one additional unit of the measure of effect [22].

The effect measure used for the health economic evaluation will be QALYs. For all patients, the effect will be estimated using the EQ-5D-5L questionnaire and the associated Danish societal weights [23].

A health sector perspective will be used to estimate the incremental costs. This means that for all patients, all costs related to healthcare services should be included. This includes inpatient and outpatient hospital services, general practitioner services, home care, and prescription medicine. Costs that are associated only with the research project that would not occur in a real-life setting will be excluded. Costs associated with the telehealthcare intervention will be calculated and included in the ICER.

Denmark is internationally known for having a comprehensive registration of data on healthcare activities. All citizens have a social security number (CPR) that is registered when in contact with a public service, such as for healthcare services. Therefore, data may be extracted for individuals to obtain a fairly accurate estimate of that individual’s use/cost of healthcare services and/or resources across municipalities, general practitioners, and hospitals.

Both deterministic and probabilistic sensitivity analyses will be conducted to assess the uncertainty of the results. A Bayesian approach will be applied using bootstrapping techniques to estimate credibility intervals for the costs and outcomes. ICERs will be estimated using second-order Monte Carlo simulations and presented in a scatterplot and a cost-acceptability curve [23].

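### Baseline adjustment depends on observed differences between the arms, and the primary comparison of change is unadjusted; the covariates, including baseline score and centre, should be fixed in advance

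*Protocol article*

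**What the plan says.** Four places in the protocol article bear on this.

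- **Statistical methods** states the adjustment rule: "If appropriate, an adjustment will be made for differences between the intervention group and the control group with regard to baseline characteristics". It names no covariate and no criterion.
- **Statistical methods, Effectiveness** sets the main analysis: "The outcome will primarily be analyzed using two-sample paired statistics". The rest of that sentence shows that changes from baseline are compared between the arms. No covariate or centre term appears.
- **Recruitment** and **Randomization** describe the design: "Recruitment takes place in three outpatient healthcare centers in the North Denmark Region". Patients are allocated from "prepacked bundles of ten envelopes, each with a card, with assignment of five patients to the intervention group and five to the control group". The bundle is handled locally: "In the outpatient healthcare center, a prepacked bundle is chosen to be the active bundle". There is a carry-over: "When three envelopes are left in an active bundle, they are shuffled into a new bundle".
- **Statistical methods, Cost assessment** gives the QALY measure: "the effect will be estimated using the EQ-5D-5L questionnaire and the associated Danish societal weights". It says nothing either way about baseline utility.

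Recruitment also shows that the KCCQ, EQ-5D-5L, SF-36 and physical measurements are taken at baseline.

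**The concern.** The rule adjusts for a variable because the arms look different on it. In a properly randomised trial that difference is chance, and its size says nothing about whether the variable predicts outcome. A covariate earns its place by being prognostic, and that can be judged before any data are seen.

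Two things are at stake. The first is discretion: the decision to adjust, and for what, is taken after the baseline data are known and possibly after the results are known, in a trial that the abstract describes as non-blinded. The second is precision: the baseline score is likely to be the strongest predictor of the follow-up score, and it enters the stated primary analysis only by subtraction, which uses it less well than regression does.

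Centre is a related case. If each centre works through its own 5:5 bundles, the arms are roughly balanced within centre by design, and an analysis that ignores centre does not use that balance.

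**Working it through.** **1. The protocol's own figure.** Inputs from Sample size: difference 5, SD 15, two-sided 5%, power 80%, 10% loss.

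- Per arm: 2 × (1.960 + 0.842)² × 15² / 5² = 141.3, so 142; total 284.
- With loss: 284 / 0.9 = 315.6, so 316.

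Both figures reproduce, and nothing below changes them.

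**2. Change score against analysis of covariance (ANCOVA).** With equal SDs σ at both visits and correlation ρ (not given in the protocol; assumed 0.3 to 0.8):

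- variance of a change score: 2σ²(1 − ρ)
- residual variance under ANCOVA: σ²(1 − ρ²)
- ratio: (1 − ρ²) / [2(1 − ρ)] = (1 + ρ)/2

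| ρ | Ratio | Variance cut |
|---|---|---|
| 0.3 | 0.65 | 35% |
| 0.5 | 0.75 | 25% |
| 0.8 | 0.90 | 10% |

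The protocol does not say whether the SD of 15 is that of scores or of changes. Power at 284 analysed, under each reading:

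| ρ | SD of scores: change | SD of scores: ANCOVA | SD of change: change | SD of change: ANCOVA |
|---|---|---|---|---|
| 0.3 | 66% | 84% | 80% | 94% |
| 0.5 | 80% | 90% | 80% | 90% |
| 0.7 | 95% | 98% | 80% | 86% |
| 0.8 | 99% | 99.7% | 80% | 84% |

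**3. How far the envelopes balance within centre.** All bundles are 5:5, so the imbalance among patients already allocated equals the imbalance among envelopes still unopened. At a bundle change three envelopes remain, so it is at most 3. Three of one kind added to a 5:5 bundle gives 8 against 5, so it can never exceed 8. Balance within centre is therefore approximate but bounded.

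**4. Simulation of that procedure.** Assumptions: 284 patients in centres of 150, 90 and 44; centre effects on follow-up only, accounting for 0%, about 7% or about 16% of follow-up variance; ρ of 0.5 and 0.7. There were 4,000 runs for type I error (simulation error about ±0.7 points) and 2,000 for power.

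- *Ignoring centre.* Type I error of the nominal 5% change test is 4.9–5.1% with no centre effect, 4.3–4.6% at a 7% share and 2.8–3.5% at 16%. With centre fitted the test is exactly 5% in theory under this model; the simulated values were 5.0–6.1%.
- *Power cost of ignoring centre* (7% share, ρ = 0.5). Change test 78.6% against 80.4% with centre; ANCOVA 88.8% against 90.3%.
- *Adjusting for the baseline score only when it differs at p < 0.05* (a threshold assumed here). Type I error is about 2–5%, so not inflated. Power at a 7% share is 80.0% against 88.8% for always using ANCOVA at ρ = 0.5, and 94.6% against 96.5% at ρ = 0.7.
- *Reporting the better of the change test and ANCOVA.* Type I error is 7.1–7.7% with no centre effect, about 6% at a 7% share and 3.6–4.6% at 16%, where ignoring centre offsets the inflation.

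**5. QALYs, on assumed inputs only.** Take utility measured twice over one year, equal SDs of 0.20 and correlation ρ. A chance baseline difference d shifts the expected QALY difference by d(1 + ρ)/2. The SE of d is 0.20 × √(2/n).

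- n = 142 per arm: SE of d = 0.0237; times 0.65, 0.80 or 0.90 (ρ = 0.3, 0.6, 0.8) gives 0.015, 0.019 or 0.021 QALY.
- n = 300 per arm (the 600 expected in the abstract): SE of d = 0.0163; the same factors give 0.011, 0.013 or 0.015 QALY.

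**The case against.** The strongest reply is that the stated primary analysis is sound and the loss is modest. That largely stands. A change-score comparison in a randomised trial is valid and already subtracts the baseline score. Ignoring centre is conservative. Even an imbalance trigger applied mechanically does not inflate the type I error. If 600 are recruited and 10% are lost, 270 per arm remain, and the change test with the protocol's SD of 15 has power Φ(5 / (15 × √(2/270)) − 1.96) = Φ(1.91), about 97%. The efficiency loss would then matter little for the main comparison.

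Several stronger readings are tempting, and the document does not support them.

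- *The false-positive rate is 7–8%.* That needs an analyst to report the better of two models, whereas the protocol names which analysis comes first.
- *The trigger has an even chance of firing.* One could count about 13 baseline variables and compute 1 − 0.95¹³ = 49%. But no significance threshold is stated, and the three quality-of-life questionnaires are not independent.
- *Randomisation is stratified by centre.* The article never says so. Drawing within centre is a fair inference from the envelope description, and the carry-over makes balance approximate.
- *Omitting centre and baseline utility are errors in themselves.* The article is silent on both, and a full analysis plan could specify them. They belong here as content of the fix.
- *Chance imbalance in utility is as large as the QALY effect sought.* The protocol states no QALY target, and the utility SD and correlation are not documented.

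What remains is the rule itself. It is stated, not merely left open, and a later plan that fixed the covariates would have to override it.

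**Conclusion.** The point holds as one of moderate weight that should be acted on. The protocol ties adjustment to observed imbalance, which is the wrong basis for choosing covariates and leaves avoidable discretion in a non-blinded trial. It also makes the less efficient of two valid analyses primary. The variance forgone is 10% to 35% for correlations of 0.8 down to 0.3, which are assumed. Omitting centre costs about 1 to 2 points of power at an assumed 7% centre share, and it errs on the conservative side. That figure also assumes that centres differ at follow-up and not at baseline; a centre difference equal at both visits would cancel from the change score. Neither the sample size nor the validity of the primary test is in question.

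**What to change.** 1. In **Statistical methods, Effectiveness**, make the primary analysis of each continuous effectiveness outcome a linear model (ANCOVA) of the follow-up value on arm, baseline value of that outcome and recruiting centre. Keep the unadjusted comparison of change as a sensitivity result. Changing the adjustment sentence alone would leave the *t* test as a contradictory primary analysis, so both places must be edited.
2. In **Statistical methods**, replace the adjustment sentence with: *Covariates are fixed in advance whatever the observed balance; none is added because of an observed baseline difference.*
3. State that mortality, which has no baseline value, takes no baseline-outcome term.
4. In **Cost assessment**, estimate incremental QALYs by regression on arm, baseline EQ-5D-5L utility and centre, and costs by regression on arm and centre, both within the bootstrap. The two differ because a QALY calculated over the whole period contains baseline utility by construction, whereas follow-up cost does not contain cost before baseline.

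The cost is wording in these places and slightly more analysis work. Baseline scores, baseline utility and centre are already recorded, and recruitment and sample size do not change. The edits should be made and dated before outcome data are examined by arm.

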#### Effectiveness

To evaluate effectiveness, differences between the intervention group and the control group with regard to SF-36 scores, mortality rates, and physical measurements from baseline to follow-up will be analyzed. The outcome will primarily be analyzed using two-sample paired statistics (e.g., two-sample paired *t* test), such that the differences from baseline to follow-up will be assessed between groups.

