**Methods/design:**

The present study is known as the TeleCare North Heart Failure Trial in Denmark. We are studying the health effectiveness and cost-effectiveness of a telehealth (Telekit) solution compared with usual care for patients with heart failure. The design is a multicenter, two-arm, parallel-group, nonblinded, superiority randomized controlled trial. Outpatient healthcare centers will be responsible for recruiting eligible participants (600 participants are expected) for the trial in the geographic area of the North Denmark Region. Participants are qualified for inclusion if they have been diagnosed according to national guidelines and are categorized in New York Heart Association class 2, 3, or 4. Patients must have a permanent residence and be motivated to use telehealth care. The primary outcomes are changes in health-related quality of life (assessed using the Kansas City Cardiomyopathy Questionnaire, the EuroQol EQ-5D-5L questionnaire, and the Short Form Health Survey [SF-36]) and in the incremental cost-effectiveness ratio measured from baseline to follow-up. The secondary outcomes are changes in mortality and in physiological indicators such as blood pressure, pulse, and weight.

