### Outcome assessments

#### Effectiveness

All outcome measures for the two groups (usual care group and the intervention group) are collected at baseline and follow-up. The primary outcome is change in health-related quality of life (SF-36 and KCCQ) from baseline to follow-up. SF-36 total score is used as the primary outcome, and the subscales are used as secondary outcomes. The secondary outcomes for effectiveness are changes in the mortality rate and physiological measurements such as blood pressure, pulse, and weight from baseline to follow-up. Mortality rate is considered only if enough participants are included to satisfy the power calculation for this secondary outcome. The clinical impact of telehealthcare is considered to be positive if no increase in mortality is observed and if pulse and blood pressure are lowered.

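### The primary analysis is labelled as a paired two-sample test, which is the wrong name for two independent arms; name an unpaired between-arm comparison, preferably ANCOVA on the baseline score

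*Protocol article*

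**What the plan says.** The abstract describes a "two-arm, parallel-group, nonblinded, superiority randomized controlled trial". The Effectiveness paragraph under Outcome assessments defines the endpoint as a change score: "The primary outcome is change in health-related quality of life (SF-36 and KCCQ) from baseline to follow-up".

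The Effectiveness paragraph under Statistical methods then names the method: "The outcome will primarily be analyzed using two-sample paired statistics". A paired two-sample t test is given as an example only. The same sentence ends with the contrast: "such that the differences from baseline to follow-up will be assessed between groups". The sentence before it lists SF-36 scores, mortality rates and physical measurements as the outcomes to be compared between the two groups.

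Baseline adjustment appears once, in the opening paragraph of Statistical methods, and is conditional: "If appropriate, an adjustment will be made for differences between the intervention group and the control group with regard to baseline characteristics". No model is named.

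The Sample size section takes "change equal to 5 for the SF-36 physical component summary" as the effect, with an SD of 15, 80% power, equal groups and a two-sided 5% level, and concludes that "the required sample size is estimated to be at least 284 participants".

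**The concern.** A paired t test needs matched observations. In this trial the only natural pairs are a patient's own baseline and follow-up scores, and a paired test on those is a before/after test within one arm, not a treatment comparison. The two arms hold different patients, so a paired test between arms is not defined. The sentence that fixes the primary analysis therefore names a procedure that cannot produce the contrast stated at its end, and the reader has to override the name to reach the intended test. The example wording also leaves the exact test open.

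Two smaller matters hang on the same text. Baseline adjustment is to be decided after looking at differences between the groups, so the primary estimate could be adjusted or not depending on the data. And mortality is listed among the outcomes while the only method given concerns change from baseline, which has no meaning for death because every patient is alive at baseline.

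**Working it through.** **1. The plan's own sample size.** Inputs from the Sample size section: difference 5, SD 15, two-sided alpha 0.05, power 80%, equal groups. For two independent means:

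n per arm = 2 × (1.96 + 0.842)² × 15² / 5² = 141.3, rounded up to 142.

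Total 284; with 10% loss, 284 / 0.9 = 315.6, rounded up to 316. Both stated figures reproduce, and power at 142 per arm is 0.802. The plan was sized for an unpaired comparison of two arms.

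**2. Which test the text describes.**
- Design: two parallel arms, so no pairing between arms.
- Endpoint: change from baseline within each patient.
- Contrast: those changes, compared between groups.
- Sizing: two independent means.

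All four point to an unpaired two-sample t test on change scores. Only the word *paired* does not fit. It most likely refers to each patient's baseline and follow-up values.

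**3. Validity of that test.** In 10,000 simulated null trials with 142 per arm and correlation 0.5, the type I error was 0.0494 for the unpaired t test on change and 0.0495 for ANCOVA. Both hold the 5% level.

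**4. What ANCOVA gains.** Let σ be the SD of the score, taken as equal at both times, and ρ the baseline to follow-up correlation. The documents do not give ρ; the values below are assumptions.
- Change-score SD = σ√(2(1 − ρ))
- ANCOVA residual SD = σ√(1 − ρ²)
- Variance ratio, ANCOVA to change score = (1 − ρ²) / (2(1 − ρ)) = (1 + ρ)/2

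The ratio is 0.65, 0.75 and 0.85 at ρ = 0.3, 0.5 and 0.7.

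**5. Power at 142 per arm, difference 5.** The Sample size section does not say whether 15 is the SD of the score or of the change, so both readings are shown. Power = Φ(5 / (SD × √(2/142)) − 1.96).

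| ρ | Score SD 15: change score (SD) | Score SD 15: ANCOVA (SD) | Change SD 15: change score | Change SD 15: ANCOVA (SD) |
|---|---|---|---|---|
| 0.3 | 66% (17.75) | 84% (14.31) | 80% | 94% (12.09) |
| 0.5 | 80% (15.00) | 90% (12.99) | 80% | 90% (12.99) |
| 0.7 | 95% (11.62) | 98% (10.71) | 80% | 86% (13.83) |

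**6. Total needed for 80% power before dropout, at ρ = 0.3, 0.5, 0.7.**
- Score SD 15: ANCOVA 258, 212, 146; change score 396, 284, 170.
- Change SD 15: ANCOVA 184, 212, 242; change score 284 throughout.

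ANCOVA needs fewer than 284 in every case.

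**The case against.** The best defence is that the sentence corrects itself. Its closing clause compares changes between groups, the endpoint is defined as change, and the sample size formula matches. On that view *paired* is a slip in an example, and a t test on change is unbiased under randomisation. This stands: the fault is one of naming, and a valid comparison can be identified. ANCOVA is not needed to make the analysis valid; writing *unpaired* would do that. A detailed model is also something an analysis plan often supplies.

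Four stronger readings are tempting, and the documents do not support them.
- **That the trial will test each arm before and after, and claim benefit if only the telehealth arm is significant.** That practice would have a badly inflated error rate, but no passage proposes it and the closing clause speaks against it.
- **That the test and the sample size conflict.** They do not once the whole sentence is read; 284 is the right figure for the stated contrast.
- **That the change-score test falls below 80% power when the correlation is under 0.5.** This holds only if 15 is the SD of the score and only 284 are analysed. The effect is expressed as a change, so an SD of change is at least as natural a reading. The abstract also expects 600 participants. After 10% loss that is 540, or 270 per arm, and at ρ = 0.3 with score SD 15 the change-score test has 5 / (17.75 × √(2/270)) − 1.96 = 1.31, which is about 90% power.
- **That the plan leaves mortality without any usable method.** Mortality is a secondary outcome, analysed only if its own power condition is met, and its method may be set elsewhere. What remains is that the sentence as worded does not suit it.

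**Conclusion.** The name of the primary test is wrong for this design and should be corrected before analysis. The intended analysis, an unpaired comparison of change between arms, is recoverable from the text, holds its error rate and agrees with the sample size. Nothing in the plan shows that the trial would reach an invalid conclusion.

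Since the sentence has to be rewritten anyway, a prespecified ANCOVA is the better replacement. It lowers the variance by 35%, 25% and 15% at correlations of 0.3, 0.5 and 0.7, whichever SD the 15 refers to, and it removes a data-dependent choice about adjusting for the baseline score. The size of the gain rests on the assumed correlation, on equal variances at the two times and on a linear relation with baseline. The direction does not depend on which SD the 15 refers to: for any correlation below 1, (1 + ρ)/2 is below 1.

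**What to change.** In the Effectiveness paragraph under Statistical methods, delete *paired* and replace the method sentence with wording such as: *The SF-36 follow-up score will be compared between the randomised arms by ANCOVA with the baseline score as a prespecified covariate, reporting the adjusted mean difference with its 95% confidence interval. The same model will be used for KCCQ, blood pressure, pulse and weight. Mortality, if analysed, will be compared directly between arms.*

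In the opening paragraph of Statistical methods, state that adjustment for the baseline score is fixed in advance, so that the conditional wording no longer governs it. In the Sample size section, say whether 15 is the SD of the score or of the change.

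If the sponsor prefers to keep change scores, the minimum is to name an independent (unpaired) two-sample t test on change from baseline.

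The cost is wording only. Baseline and follow-up values are already collected, and the stated 284 (316 with loss to follow-up) need not rise.
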